
**Figure 1 F1:**
[figure not shown]
Study flow chart. EEG, electroencephalography; tACS, transcranial alternating current stimulation; T, treatment; V, visit.

**Table 1 T1:** Overview study procedures

Procedures (time needed)	Baseline visit (V1)	First treatment visit (T1)	Additional treatment visits (T2 up to T14)	Post-treatment visit (V2)	Follow-up visit (V3)
Medical history*	X				
Physical health*	X				X
Current medication use*	X	X	X	X	X
Clinical Frailty Scale*	X				
Sensation questionnaire (5 min)		X		X	
Blinding and subjective treatment experience (1 min)		X		X	
Feasibility questionnaire (5 min)		X			
Delirium interview (10 min)	X				
ICDSC (10 min)	X	X	X	X	
DOSS (5 min)†	X	X	X	X	
TICS-M (10 min)					X
EEG (40 min)	X‡	X		X	
tACS (30 min)		X	X		
Estimated total duration	25 or 60 min‡	95 min	45 min	65 min	15 min

* This information will be recorded as part of standard clinical care, and missing information will be requested via family and will therefore not require additional time.

† Only non-intensive care unit () patients will be assessed using the DOSS.

‡ Only the group randomised to personalised tACS will receive an EEG during the baseline visit.

DOSS, Delirium Observation Screening Scale; EEG, ElectroencephalogramICDSC, Intensive Care Delirium Screening Checklist; tACStranscranial altering current stimulationTICS-M, Telephone Interview for Cognitive status, modified version

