### Intervention

tACS will be administered to participants who are randomised using the Nurostym tES device (Brainbox, UK) by a trained member of the study team. The same tACS device and settings will be used across all three participating centres to ensure consistency of results. For all study arms, tACS will be administered at an intensity of 2.0 mA (peak to peak) for 30 min using two 5×5 cm saline-soaked electrodes while the impedance is kept below 10 kΩ. Electrode placement (described below) follows the 10–10 EEG system, ensuring consistent positioning of tACS electrodes across different stimulation days, patients and centres. The electrodes will be positioned beneath a 64-channel EEG cap. During the first treatment session, this cap will also be used for repeated EEG measurements, whereas on subsequent treatment days, it will serve solely as a reference for tACS electrode positioning. Treatment with psychoactive medication(s) that is deemed necessary for the participant will be continued as prescribed by the treating physician.

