### Outcomes

#### Pilot study outcomes

During the pilot phase, data regarding the percentage of fully completed tACS sessions will be recorded as well as increased care requirements within 1 hour following tACS administration. An increase in care requirement is defined as a (medication-based) intervention (eg, for heightened agitation or skin issues resulting from the electrodes), fixation, or transfer to unit with more advanced care (eg, the intensive care unit). Furthermore, duration of delirium will be recorded as defined in the secondary outcomes below. On analysis of these findings, adjustments to the protocol may be proposed and will be submitted to the Medical Research Ethics Committee (MREC) for approval before the start of the main study phase, if deemed necessary.

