##### Secondary outcomes

Delirium duration assessed by the number of days with delirium during the treatment period (up to 14 days). A delirium-positive day is defined as having an Intensive Care Delirium Screening Checklist (ICDSC)^51^ score of ≥4. A score of –4 or lower on the RASS followed by an ICDSC score ≥4 is counted as a delirium day. For days where ICDSC is missing (eg, due to limited staff availability on some weekends), days with a Delirium Observation Screening Scale (DOSS)^52^ score ≥3 will also count as a delirium day. The DOSS is administered as standard of care.Delirium severity as assessed by the cumulative ICDSC score per participant recorded on days with delirium during the treatment period. In instances where ICDSC scores are unavailable, scores will be estimated using information from the electronic patient record.Quantitative EEG measures include peak frequency, spectral analysis and connectivity measures such as the phase lag index,^53^ corrected amplitude envelope correlation^48^ and topological measures based on the minimum spanning tree.^54 55^Length of hospital stay as assessed by the total number of days admitted to the hospital.Cognitive status 3 months after the first tACS session as assessed by the TICS-M.^43 44^Presence and duration of sensations related to tACS treatment including tingling sensations, itching, mild transient redness of the skin and discomfort on the region of stimulation with the sensation questionnaire developed for this study (online supplemental appendix 1).The treatment burden, perception of receiving either sham or active tACS and patients’ perceptions of the therapeutic relationship with the researcher(s) will be evaluated using the questionnaires on feasibility, or blinding and subjective treatment experience, which have been developed for this study (online supplemental appendix 1).

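### Days at RASS -4 or lower with no later positive ICDSC add nothing to delirium duration or severity, so a difference between arms in deep sedation or coma would read as less delirium

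*Protocol article*

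**What the plan says.** All places are in the protocol article.

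- **Duration (Secondary outcomes).** The outcome is a plain count: "Delirium duration assessed by the number of days with delirium during the treatment period (up to 14 days". A day is positive when the ICDSC is 4 or more.
- **Deep sedation or coma (same section).** "A score of –4 or lower on the RASS followed by an ICDSC score ≥4 is counted as a delirium day". The text does not say how soon the later score must come, or how the day is classed if the later score is below 4 or never obtained.
- **Missing ICDSC, duration (same section; Table 1 footnote).** A DOSS of 3 or more then also makes a delirium day, but the footnote limits the instrument to patients outside intensive care: only those "patients will be assessed using the DOSS".
- **Severity (same section).** "Delirium severity as assessed by the cumulative ICDSC score per participant recorded on days with delirium during the treatment period". Unavailable ICDSC scores are to be estimated from the patient record.
- **Resolution (Study design and setting).** Two negative assessments in a row define resolution, which ends treatment. Whether a day at RASS -4 or lower is negative or unassessable is not stated.
- **Entry (Inclusion criteria for eligibility).** RASS must lie between -2 and +2.
- **Medication (Intervention).** "Treatment with psychoactive medication(s) that is deemed necessary for the participant will be continued as prescribed by the treating physician".
- **Pilot (Pilot study outcomes; Interim analysis).** Delirium duration is compared between active and sham, and the results go to the ethics committee before the main phase.

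**The concern.** Every participant is randomised with confirmed delirium and a RASS of at least -2. A later day at RASS -4 or lower therefore arises after inclusion, and may reflect deterioration, sedating medication or another cause. It is not evidence that thinking has cleared. Yet unless a positive ICDSC follows, or the DOSS route applies, the count gives it the value of a clear day. The same holds for a patient whose observation ends while still in that state.

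Severity inherits the problem because it is summed over delirium days only. A day that is not classed as delirium never enters the sum, and the record-based estimate, read as written, fills in scores only on days already in it.

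At stake is the direction of two secondary clinical outcomes, and of the pilot comparison of duration, if stimulation changes how often patients become deeply sedated or comatose. The article itself counts medication for heightened agitation and transfer to more advanced care among the increased care requirements to be recorded after tACS, so a difference between arms is at least conceivable.

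**Working it through.** The article states no expected value, SD or frequency for delirium duration or severity. Its sample size concerns relative delta power and does not enter here, so there is no figure of the plan's own to reproduce. The check applies the written rule to assumed day sequences.

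**Scoring inputs**
- P: ICDSC of 4 or more (set to 6 for illustration). Adds 1 day and 6 points.
- N: ICDSC below 4. Adds 0.
- C: RASS -4 or lower with no ICDSC that day and no qualifying DOSS. Adds 1 day only if a positive ICDSC follows.

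**Step 1. Rule applied to single patients**

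| Sequence | Duration under the rule | Severity under the rule | Days with P or C |
|---|---|---|---|
| PPPPPPNN | 6 | 6 × 6 = 36 | 6 |
| PPPCCCNN | 3 | 3 × 6 = 18 | 6 |
| PPPCCC (observation ends) | 3 | 18 | 6 |
| PPCPPPNN | 6 | 5 × 6 = 30, plus a record-based estimate for C | 6 |
| PPPCCCPN | 5 or 7 | 4 × 6 = 24, plus estimates for each counted C | 7 |

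Rows 2 and 3 show the gap: each C day scores as an N day would. Row 4 shows the rule working when a positive score follows. Row 5 shows the missing window. If the positive score must come the next day, only the last C counts (4 + 1 = 5). If it covers the whole run, all three count (4 + 3 = 7).

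**Step 2. Shift in the difference between arms**

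Let q be the share of patients with uncounted C days in each arm, and u the number of such days per affected patient. Then

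shift = (q_active − q_sham) × u.

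- Equal shares: 0 × u = 0.
- Assumed 5% v 2%, u = 2: 0.03 × 2 = 0.06 day.
- Assumed 10% v 2%, u = 2: 0.08 × 2 = 0.16 day.
- Wider range, differences of 5 to 30 percentage points and u from 1 to 3: 0.05 × 1 = 0.05 day up to 0.30 × 3 = 0.9 day.

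The shift favours whichever arm has more such days.

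**Step 3. The pilot**

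Thirty patients at 1:1 give about 15 per arm. One additional patient with 2 uncounted days in one arm moves that arm's mean by 2 / 15 = 0.13 day.

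**The case against.** - **The text never calls these days delirium-free.** That is right: it is silent on the case, and the article is a condensed document. But a specific condition is stated, and in a plain count an uncounted day adds zero. The consequence follows from the definition as published.
- **The rule already covers the patient who is sedated and wakes still delirious.** True, and this narrows the gap to days followed by a score below 4 or by no score. Leaving out a sedated day that precedes a negative score is defensible for an outcome named delirium duration. The delirium-only count should therefore stay.
- **Severity has a fallback.** The record-based estimate helps for coma days that count as delirium days. It does not reach days left out of the sum. How many points are lost is unknown, because an unassessable day has no observed score.
- **Such days may be few.** Entry at RASS -2 to +2 makes this plausible, and no frequency is given. Increased care requirements in the pilot and increased antipsychotic use as an adverse event are recorded separately, so a difference would not be wholly hidden.

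A reader might infer that the plan rewards rescue sedation. The documents do not support that: the term does not appear, medication for agitation is only an example within an outcome definition that also names skin problems, and necessary psychoactive treatment is described as continued, not as unrestricted. A reader might also infer that duration decides whether the main phase starts. The outcomes and interim sections give no threshold for it and say only that results are shared with the ethics committee.

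**Conclusion.** The concern holds as a gap in an outcome definition. A day at RASS -4 or lower with no later ICDSC of 4 or more, and no qualifying DOSS outside intensive care, contributes nothing to duration or cumulative severity and cannot be told apart from recovery. The undefined window alone can change one patient's count (5 or 7 days in the last sequence).

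Bias between arms is conditional. It needs a difference in such days, it is zero without one, and it is 0.06 to 0.16 day on a count of at most 14 under the two main assumed scenarios, neither of which comes from the documents. Two secondary outcomes and the pilot comparison of duration are exposed; the primary EEG outcome is not. The change is worth making because it is cheap and the rule already depends on RASS, not because a large bias has been shown.

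**What to change.** 1. Keep the delirium-only count as the named outcome, and define the window that the later ICDSC must fall in, including whether it covers a whole run of days at RASS -4 or lower.
2. Add a prespecified companion analysis of days with delirium or coma, in which every day at RASS -4 or lower counts whatever ICDSC follows. Use it in both the pilot comparison and the main analysis.
3. Show the number of days at RASS -4 or lower by arm beside the duration and severity results. For severity this is disclosure only. Averaging the ICDSC over assessable days would not recover the missing days either.
4. Reconcile the handling of these days under Secondary outcomes with the definition of resolution under Study design and setting. No rule is proposed here, because resolution ends treatment.

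**Cost.** No new measurement is needed if RASS is kept in the daily record, as the present rule requires. Recruitment is under way, so a small amendment to the outcome wording is needed. The companion count mixes drug-induced coma with delirium, which is why it should stand beside the delirium-only count and not replace it.

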### Study design and setting

This study is a double-blind, RCT conducted across three medical centres in the Netherlands: the University Medical Center (UMC) Utrecht, Radboud UMC and HagaZiekenhuis. To assess safety and feasibility of tACS in delirious patients, the study will start with a pilot phase in which 30 patients will be randomised in a 1:1 ratio to receive daily either standardised active tACS or sham treatment for a maximum of 14 days, or until resolution of delirium or hospital discharge.

On completion of the pilot phase, the main study phase will begin, introducing the personalised treatment arm. Criteria for continuing to the main study phase are defined under outcomes. All patients from the pilot phase will be included in the main study analyses. Randomisation weights will be recalculated, and participants will be allocated in an overall 1:1:1 ratio to receive either standardised tACS, personalised tACS, or sham treatment (ie, combining personalised sham and standardised sham tACS into one arm). The baseline visit will include delirium assessment using the Delirium Interview,^41^ administered by a trained researcher, and reviewed by an expert delirium panel. Furthermore, information will be collected from the electronic patient record and the Clinical Frailty Scale^42^ will be evaluated. After these assessments, the first treatment session starts which includes a 64-channel EEG measurement before and after the first tACS or sham treatment. Also, a questionnaire on sensation to assess possible adverse events (AEs) of tACS, a questionnaire on feasibility and questionnaire on blinding and subjective treatment experiences (online supplemental appendix 1) will be administered. Following this, daily tACS or sham treatment visits and delirium assessments will take place for a maximum of 14 days, or until resolution of delirium or hospital discharge, whichever comes first. To account for fluctuations in delirium symptoms, resolution of delirium is defined as two consecutive negative delirium assessments. The treatment phase will end with a close-out visit including a follow-up 64-channel EEG and administration of the questionnaires on sensation, blinding and subjective treatment experiences. A brief cognitive assessment using the Telephone Interview for Cognitive status, modified version (TICS-M)^43 44^ is planned at 3 months after the first tACS session. The study design is illustrated in figure 1, and the study schedule is presented in table 1.

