### Sample size and statistical power

The sample size calculation is based on data obtained from a previous study that examined EEG findings in both delirious and non-delirious patients.^15^ In this study, patients with delirium showed a median relative delta power of 0.59 (IQR 0.47–0.71), while those without delirium had a median of 0.20 (IQR 0.17–0.26), resulting in an effect size of 0.39 (0.20–0.59). This study excluded patients in whom the diagnosis delirium was not certain, which may have inflated the effect size. It is therefore anticipated that both standardised and personalised tACS will lead to a more modest decrease of 0.15 in relative delta EEG power poststimulation compared with prestimulation measurements. We hypothesise that personalised tACS may be superior to standardised tACS in reducing relative delta power. However, the lack of data to support this claim necessitates assuming equal effectiveness for both arms in the sample size calculation. Based on these assumptions, a sample size of 159 participants (ie, 53 per group) was estimated using G*Power 3.1. This estimation considered an effect size of 0.15 with a SD of 0.3, an alpha of 0.05 and 80% statistical power. Patients who do not complete the initial tACS session with EEG recordings will be replaced, as well as patients who withdraw consent.

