#### Exclusion criteria for eligibility

A potential participant who meets one or more of the following criteria will be excluded from participation in this study:

Inability to conduct valid delirium screening assessment (eg, deaf, blind) or inability to speak Dutch or English.A moribund state.Alcohol/substance abuse withdrawal or stroke as the presumed cause of delirium.Diagnosis of dementia, based on medical record review and/or a score of ≥4.5 on the short form of the Informant Questionnaire on Cognitive Decline in the Elderly.^46^Brain injury of any type (eg, traumatic, vascular, post anoxic) in the previous 6 weeks.One or more contraindications for tACS:Large or ferromagnetic metal parts in the head (except for a dental wire).Implanted cardiac pacemaker or neurostimulator.Skin disease or inflammation at the stimulation sites.History of epilepsy.

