Delirious patients who meet all inclusion criteria but none of the exclusion criteria for eligibility and randomisation will be randomised to one of the study arms. Randomisation will be conducted electronically via the Castor Electronic Data Capture (EDC) study management system (Castor, Ciwit B.V., Amsterdam, the Netherlands), using a validated block randomisation model, stratified by study centre. In the pilot phase, standardised active tACS and sham carry equal weight (1:1). Patients will be randomised with block sizes of 2 and 4. In the main study phase, four groups will be created in Castor EDC (standardised active, personalised active, standardised sham, personalised sham) with different weights, depending on the number of participants who have been randomised to the active and standardised sham groups during the pilot phase. As the first 30 patients are included during the pilot phase, randomisation weights will be 3, 4, 1 and 2, respectively. These numbers are chosen to closely match the overall 1:1:1 allocation. Randomisation will be performed with block sizes of 10 and 20, which are randomly selected.

Following randomisation, a designated study team member not involved in any other study procedures or data analysis will be aware of the randomisation outcome. This person will have access to a list of codes that permits the tACS device to deliver active or sham stimulation. Participants and all other study staff will be blinded to whether active or sham stimulation is applied. To ensure blinding during the intervention, the monitor displaying the raw ECG traces will be covered with cardboard paper before the start of the procedure for patients on continuous ECG monitoring. Due to the additional EEG required in the personalised treatment arm, blinding with regard to receiving standardised or personalised tACS will not be possible. However, EEG preprocessing and data analysis will be performed blinded for treatment allocation.

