### Statistical analysis

For the analysis of the primary study parameter, a per-protocol analysis will be used. The sole criterion for inclusion in the analysis is that a participant has completed the initial tACS session and EEG recordings. Changes in relative delta power will be assessed using separate linear mixed models for standardised and personalised tACS compared with sham, with relative delta power as the dependent variable, time*group and study centre as fixed factors, and participant as a random factor. Data analysis will be performed blinded for treatment allocation. A significance level of p=0.05 (two-tailed) will be applied. To retain sensitivity to detect potential effects in this novel area of research, no adjustment for multiple comparisons will be made. In cases of deviations from the linear mixed model, robust models and non-parametric alternatives will be considered. Subgroup analysis will be conducted by including additional fixed factors to the mixed models, such as delirium aetiology, sex and age. Functional outcomes, along with other quantitative EEG measurements and cognitive outcomes, will be analysed using non-parametric or parametric tests depending on the distribution of scaled test results. Blinding success for participants as well as researchers will be tested using a χ^2^ test.

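### Scoring the short IQCODE in every participant, and adjusting the 3-month TICS-M for it, age and centre, would cheaply sharpen a comparison that is already valid

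*Protocol article*

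**What the plan says.** - **Outcome.** Under Secondary outcomes the protocol article lists "Cognitive status 3 months after the first tACS session as assessed by the TICS-M". Study design and setting describes the same brief assessment, which "is planned at 3 months after the first tACS session". Table 1 marks TICS-M once, at the follow-up visit V3.
- **Baseline.** At V1, Table 1 has medical history, physical health, medication, the "Clinical Frailty Scale", the Delirium Interview, the two delirium scales and, for the personalised group, an EEG. None of these is a score of cognition before the delirium.
- **IQCODE.** It is named once, under Exclusion criteria for eligibility: "Diagnosis of dementia, based on medical record review and/or a score of ≥4.5 on the short form of the Informant Questionnaire on Cognitive Decline". As worded, record review alone is enough, so the score need not be obtained in everyone.
- **Randomisation.** It is done "using a validated block randomisation model, stratified by study centre".
- **Analysis.** The primary outcome gets linear mixed models with centre as a fixed factor. Other outcomes, including the "cognitive outcomes, will be analysed using non-parametric or parametric tests depending on the distribution of scaled test results". No covariate and no centre term is named for them.

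**The concern.** Participants are delirious at enrolment, so a TICS-M taken at V1 would reflect the delirium rather than the patient's usual cognition. An informant measure is the practical substitute, and the plan already names one. Because only dementia and IQCODE scores of 4.5 or more are excluded, patients with lesser prior decline can enter. How far they had declined beforehand plausibly explains part of the spread in TICS-M at 3 months.

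If the score is not kept for everyone, two things are given up. One is precision on the only listed outcome measured at 3 months, which is also a stated secondary objective. The other is context: a low TICS-M cannot easily be read as new impairment or as long-standing decline. An analysis plan can add a covariate later, but it can use only scores that were recorded.

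**Working it through.** **Inputs from the protocol article.** 53 participants per arm ("a sample size of 159 participants (ie, 53 per group) was estimated using G*Power 3.1"), two-sided alpha 0.05 and 80% power.

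**Assumed, because the documents give no value.** The correlation r between IQCODE and 3-month TICS-M (absolute value), taken as 0.2 to 0.6; a reference difference of 0.5 SD in TICS-M; and 20% loss by 3 months.

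**The plan's own figure.** 159 is reproduced by a three-group one-way ANOVA with f = d/2 = (0.15/0.3)/2 = 0.25, which gives power 0.805. It concerns relative delta power. No power is claimed for TICS-M, and only the 53 per arm is used below.

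**Step 1: precision without adjustment.** Minimum detectable difference in SD units = (1.960 + 0.842) × √(2/53) = 2.802 × 0.194 = 0.544.

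**Step 2: precision with one baseline covariate.** Residual variance is multiplied by (1 − r²), the detectable difference by √(1 − r²), and the effective number per arm is 53/(1 − r²).

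| r | Variance removed | Detectable difference (SD) | Power for 0.5 SD | Effective n per arm |
|---|---|---|---|---|
| 0 | 0% | 0.544 | 0.73 | 53 |
| 0.2 | 4% | 0.533 | 0.75 | 55 |
| 0.3 | 9% | 0.519 | 0.77 | 58 |
| 0.4 | 16% | 0.499 | 0.80 | 63 |
| 0.5 | 25% | 0.471 | 0.84 | 71 |
| 0.6 | 36% | 0.435 | 0.90 | 83 |

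**Step 3: losses before V3.** Participants are replaced only if they do not complete the first session with its EEGs or withdraw consent, so deaths and losses reduce the TICS-M sample. At 20% loss (53 × 0.8 ≈ 42 per arm) the detectable difference is 0.611 SD unadjusted, 0.599 at r = 0.2 and 0.489 at r = 0.6.

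**Step 4: chance imbalance.** For two arms of 53, the difference in mean baseline has SD √(2/53) = 0.194 baseline SD, with a 95% range of ±0.38. The chance that it exceeds 0.2 SD in either direction is about 30%. An imbalance of 0.2 SD moves the TICS-M contrast by r × 0.2, that is 0.04 SD at r = 0.2 and 0.12 SD at r = 0.6. The unadjusted standard error already allows for this.

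**The case against.** The case for leaving the plan alone has several parts.

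- **Validity.** The objective is a comparison with sham, and randomisation makes a follow-up-only comparison sound. A reader might infer from the missing baseline that the cognitive result would be biased. The documents do not support that. This part stands in full. Separating new from prior impairment is not a stated objective either.
- **Silence is not omission.** A reader might also infer that the IQCODE goes unscored. Table 1 is not exhaustive: the RASS has no row, yet it is needed for eligibility and for counting delirium days. The full protocol or the case report form may record the score in everyone. This stands too, so the point is only that the article does not require it.
- **Analysis detail.** A reader might take the plan to commit to raw scores and an unadjusted two-group test. The article says neither. It names a family of tests, and covariates for a secondary outcome are commonly fixed in the analysis plan. Collecting the score is the part that belongs in the protocol.
- **Size.** No correlation is given. The IQCODE measures decline while TICS-M measures status, and excluding high scores narrows its range; both may lower r. Age is already named as a factor for subgroup analyses, and frailty is recorded at V1. What IQCODE adds beyond those would ordinarily be less than the table shows.
- **Urgency.** An informant can be asked later, so the baseline is not lost for good. Such a score is less clean, because the informant has by then seen the delirium and its aftermath.

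**Conclusion.** The point holds as a low-cost improvement to a secondary outcome. It is not a mistake or a contradiction, and the absence of a baseline does not bias the comparison between arms. On the article's wording, a pre-delirium cognitive score need not exist for every participant, and the named test uses neither a baseline covariate nor the stratification factor.

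The gain depends wholly on an assumed r. At 0.2 it is slight: 4% of variance, and a detectable difference of 0.533 instead of 0.544 SD. At 0.6 it is worthwhile: 36% of variance and 0.435 SD. These figures compare adjustment with none, so they overstate what IQCODE adds if age and frailty are used anyway.

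**What to change.** 1. Obtain the short IQCODE at V1, before randomisation, for every participant with an available informant. Record the score itself and not only the exclusion decision, and add a row to Table 1. Reword the dementia criterion so that record review does not replace the score where an informant exists. If the full protocol already does this, only the article's wording and table need to change.
2. Analyse TICS-M with a linear or rank-based model adjusted for study centre, age and IQCODE.
3. Where IQCODE is missing, keep the participant, for example by single imputation of this baseline covariate without reference to arm.

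**Cost.** A few minutes from a relative or representative who is in most cases already being approached for consent, one table row and one sentence on analysis. Some scores will be missing, and those gathered retrospectively for patients already enrolled will be less clean. The Outcomes section already allows protocol adjustments, with ethics committee approval, before the main phase, and 129 of the 159 participants belong to that phase.
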